### Participant timeline

The follow-up period for this trial is 28 days. At the final visit of the last patient, data regarding the clinical status of all participants who have either completed the trial or withdrawn will be collected.

### Sample size

In this study, the primary efficacy endpoint was the 28-day all-cause mortality rate. A large-scale epidemiological survey conducted in the ICU revealed that the control group had a 38.2% 28-day all-cause mortality rate. In an RCT comparing the LA injection treatment group, the relative risk reduction was approximately 0.33.^38^ The anticipated 28-day all-cause mortality rate for the treatment group was expected to be 22.9% with a one-sided test, using α=0.025 and β=0.2 (power=80%). The threshold value, Δ, was set at 0.

Participants are randomised at a ratio of 1:1, resulting in a calculated sample size of 160 for each group using a superiority test (where a lower rate is considered superior). Taking into account the anticipated dropout rate of around 10%, the sample size was increased to 176 cases in each group.

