In a study conducted by Zhang *et al*,^17^ it was demonstrated that LA effectively attenuates lipopolysaccharide (LPS)-induced acute inflammatory responses both in vitro and in vivo. This attenuation is achieved through the activation of the phosphoinositide 3-kinase (PI3K)/protein kinase B (Akt) signalling pathway. Multiple studies^18–21^ have demonstrated that LA possesses anti-inflammatory properties and can effectively reduce LPS-induced inflammation. LA achieves this by inhibiting the activation of the nuclear factor κB (NF-κB) signalling pathway and suppressing the excessive production of proinflammatory factors. These actions contribute to the attenuation of sepsis-induced inflammation and oxidative damage in organs, highlighting the potential of LA as a therapeutic intervention for sepsis. Furthermore, LA has shown significant benefits in improving diabetic neurovascular and metabolic abnormalities.^22^ Additionally, it has been implicated in cardiovascular protection and exerting anti-inflammatory effects.^23–26^ This suggests that LA may have broad therapeutic applications beyond sepsis treatment. Considering its anti-oxidative properties, LA holds promise as a potential adjuvant for sepsis treatment. Its ability to protect tissues from oxidative stress and prevent sepsis-induced organ dysfunction makes it a candidate worth exploring further.

Indeed, LA has been investigated in various therapeutic contexts, including weight management,^27 28^ multiple sclerosis,^29^ male fertility^30^ and type 2 diabetes,^31 32^ showing promising results. However, when it comes to sepsis-induced organ dysfunction, most studies have primarily focused on animal models, particularly rats.^17 33 34^ As of today, there is a lack of human studies exploring the therapeutic effects of LA in sepsis treatment.

To address this gap in knowledge, we have designed a multicentre, single-blinded, randomised controlled trial (RCT) in China. The objective of this trial is to assess the efficacy and safety of LA injection compared with a placebo in patients diagnosed with sepsis or septic shock in ICUs. We aim to investigate the preventive and therapeutic effects of LA on suppressing inflammation, attenuating organ dysfunction, shortening ICU or hospital stay and improving patient outcomes, including mortality. By conducting this RCT, we hope to provide valuable insights into the potential benefits of LA in sepsis treatment.

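### The sample size paragraph pairs a relative risk reduction of about 0.33 with a treatment-arm mortality of 22.9%, which is a reduction of 0.40; the stated 80% power fits neither figure

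*Protocol article*

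**What the plan says.** All the figures stand in the Sample size section of the protocol article. It confirms that "the primary efficacy endpoint was the 28-day all-cause mortality rate" and, from a large epidemiological survey in intensive care, that "the control group had a 38.2% 28-day all-cause mortality rate". The next sentence gives the evidence for the effect: "In an RCT comparing the LA injection treatment group, the relative risk reduction was approximately 0.33". The sentence after that gives the design rate: "The anticipated 28-day all-cause mortality rate for the treatment group was expected to be 22.9" (per cent), together with a one-sided test at 0.025, 80% power and a margin of zero. Allocation is 1:1, "resulting in a calculated sample size of 160 for each group using a superiority test". Finally, "Taking into account the anticipated dropout rate of around 10%, the sample size was increased to 176 cases in each group", which makes the 352 patients in the abstract.

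No other section gives a reason for 22.9% or a second source for the treatment effect.

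**The concern.** Two of the three quantities (control rate, relative reduction, treatment rate) fix the third. Here all three are stated and they do not fit together. A reader who follows the cited evidence arrives at 25.6%, yet the rate stated alongside alpha and power is 22.9%. The absolute difference to be detected is then 15.3 percentage points instead of 12.6.

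This matters because 28-day mortality is the primary endpoint, no interim analysis is scheduled, and the article presents the sample size as a strength. Readers of a neutral result will use the stated power to judge how much benefit the trial could have missed. If the evidence-based effect is the 0.33 reduction, that power is well below 80%.

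**Working it through.** **Inputs** (all from the Sample size section): control rate p1 = 0.382; relative risk reduction about 0.33; treatment rate 0.229; one-sided alpha 0.025 (z = 1.960); power 80% (z = 0.842); margin 0; 1:1 allocation; 160 per arm, raised to 176.

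**Step 1. Do the rates agree?**
- From the cited reduction: 0.382 × (1 − 0.33) = 0.2559, or 25.6%.
- From the stated rate: 1 − 0.229/0.382 = 0.4005, a reduction of about 0.40.
- Rounding does not close the gap: even a reduction of 0.35 gives 0.382 × 0.65 = 24.8%.

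**Step 2. Can the plan's 160 be reproduced from its own rates?**

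Pooled-variance formula: n = [1.960 × √(2p̄(1 − p̄)) + 0.842 × √(p1(1 − p1) + p2(1 − p2))]² / (p1 − p2)², where p̄ is the mean of the two rates.

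For 0.382 vs 0.229: p̄ = 0.3055, the square roots are 0.6514 and 0.6424, and the difference is 0.153. This gives n = 141.1, so 142 per arm.

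| Method, 38.2% vs 22.9% | n per arm for 80% power |
|---|---|
| Unpooled normal | 139 |
| Arcsine | 141 |
| Pooled normal | 142 |
| Log odds ratio | 145 |
| Log relative risk | 150 |
| Fisher's exact | about 153 |
| Pooled with continuity correction | 154 |

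None gives 160. The stated number is larger than all of them, so at 22.9% it is on the safe side. For 0.382 vs 0.2559 the pooled formula gives 213.4, so 214 per arm, and 229 with continuity correction. So 160 does not come from the 0.33 reduction either.

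**Step 3. What power does the planned size give?**

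Power = Φ{[(p1 − p2)√n − 1.960 × √(2p̄(1 − p̄))] / √(p1(1 − p1) + p2(1 − p2))}.

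- At 22.9%, n = 160: (0.153 × 12.649 − 1.960 × 0.6514)/0.6424 = 1.025, and Φ(1.025) = 84.7%.
- At 25.6%, n = 160: (0.12606 × 12.649 − 1.960 × 0.6591)/0.6531 = 0.463, and Φ(0.463) = 67.8%.

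| Treatment rate | n per arm | Pooled normal | Continuity-corrected | Fisher |
|---|---|---|---|---|
| 22.9% (reduction 0.40) | 160 | 84.7% | 81.7% | 82.0% |
| 22.9% | 176 | 87.9% | 85.4% | 85.6% |
| 25.6% (reduction 0.33) | 160 | 67.8% | 63.4% | 63.8% |
| 25.6% | 176 | 72.0% | 68.0% | 68.1% |

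**Step 4. At what effect does 160 per arm give 80% power?**

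Solving the pooled power equation for p2 at n = 160 gives a treatment rate of 23.8%, and 1 − 0.238/0.382 = 0.38. This lies between the two effects and is not stated in the article.

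**The case against.** The strongest reply is that 22.9% is the design assumption. It is the rate that the article states in the same sentence as alpha, beta and power, and at that rate 160 per arm delivers more than 80% whichever standard test is used. The article never says that 22.9% was calculated from 0.33; the two merely stand in adjacent sentences. A design may also target a larger effect than an earlier trial found.

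Most of this stands. A reader might infer that the true power is simply 68% and that the trial is underpowered. The document does not support that as a fact: it holds only if 0.33 is the intended basis, and nothing shows which figure is the misprint. Even then, 68% applies to 160 per arm. The analysis is by intention to treat and the Participant timeline section collects status for withdrawn patients too, so loss may be small and power nearer 72%.

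Three further readings are tempting but are not part of this point:
- **The dropout step.** 160 × 1.10 = 176, whereas 160/0.90 = 178. But 176 allows for a loss of 16/176 = 9.1%, which is fairly described as around 10%.
- **The unnamed formula behind 160.** A journal article commonly leaves this to the full protocol.
- **The origin of the 0.33.** The Introduction says that human studies of lipoic acid in sepsis are lacking, so one might conclude that the cited trial was in another disease. That trial is not shown, and the arithmetic does not depend on it.

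What the reply does not remove is the contradiction. If 22.9% is deliberate, the article sizes the trial on a 40% relative reduction in mortality directly after citing 33%, and does not say so.

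**Conclusion.** The paragraph is wrong as written. A control mortality of 38.2%, a relative reduction of about 0.33 and a treatment mortality of 22.9% cannot all hold. The 80% power stated for 160 per arm matches neither reading: about 68% (72% with all 176) if 0.33 governs, and about 82–85% if 22.9% governs.

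These figures assume that the 38.2% control rate is correct, a one-sided 0.025 test and equal arms. The 68% and 72% use the normal approximation; with a continuity correction or Fisher's test they become about 63–64% and 68%. The inconsistency itself rests on no assumption about the test.

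**What to change.** Amend the Sample size section so that the three rates agree, and restate the power. The investigators know which figure was intended. Either:

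1. keep the 0.33 reduction, give the treatment rate as 25.6%, and state power of about 68% with 160 per arm (72% with 176); or
2. keep 22.9%, state that the design targets a relative reduction of 0.40, larger than the 0.33 of the cited trial, give the reason, and state power of about 82–85% with 160 per arm.

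In both cases add that 160 per arm gives 80% power only at a treatment rate of about 23.8% (relative reduction about 0.38), and that power at the cited 0.33 reduction is about 68–72%.

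The cost is a text amendment. Enrolment, endpoint and analysis do not change. Under the first option the published power becomes less favourable; under the second the larger target effect has to be defended.

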### Recruitment

To achieve adequate participant enrolment and reach the target sample size, the trial is planned to be conducted in multiple tertiary hospitals as outlined in table 1. The enrolment period is estimated to span 2 years. The study successfully recruited its first participant on 26 August 2021. A well-trained study coordinator has been appointed at each participating centre to meticulously screen all potentially eligible patients based on the predefined eligibility criteria. The anticipated timeline for completion of the study is set for 1 September 2024.

### Consent and assent

The clinical investigator has the responsibility to obtain informed consent from every research subject prior to their participation in the study. Detailed information about the informed consent can be found in online supplemental appendix 1. In cases where a research subject is unable to provide consent due to a critical illness or disability, informed consent is obtained from authorised surrogates. However, it is important to note that obtaining prior approval from the EC is necessary for this process. Our intention is solely to obtain consent for the use of data and samples related to the research question outlined in this protocol. We do not have any plans to utilise participant data or biological samples for ancillary studies.

10.1136/bmjopen-2023-072897.supp1Supplementary data

### Allocation

In this study, participants who have been diagnosed with sepsis based on the Sepsis-3 criteria are included in the screening process. Those who meet the eligibility criteria will be randomly assigned to either the treatment or control group using a 1:1 allocation. The randomisation will be conducted using a computer-generated block randomisation schedule with a block size of 8, stratified by site. Each block will consist of four patients receiving the LA injection and four patients receiving a placebo. The randomisation method and block size will not be blinded until all data analysis is completed. The investigators involved in the study will not participate in data collection. The randomisation centre, through net verification, will assign the screened patients at each hospital in a random manner.

To ensure the overall quality and integrity of the clinical trial, code breaks should only occur in exceptional circumstances when knowledge of the actual treatment is absolutely necessary for further patient management. Investigators are encouraged to consult with medical advisors if they believe that unblinding is necessary. Any instances of code breaks must be reported, along with the reason, on the corresponding CRF page. It is important to note that unblinding should not automatically result in the discontinuation of the study drug.

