**Trial registration:**

ChiCTR2000039023.

Strengths and limitations of this studyThe trial utilises a randomised controlled design with a substantial sample size.The trial design mitigates the influence of confounding factors, such as terminal diseases.Adequate evidence from animal and human research supports the hypothesis that lipoic acid could protect organs against sepsis injury.This trial follows a single-blind study design rather than a double-blind design.

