### Interventions

The participants will be randomly assigned to either the placebo group or the LA group and treated according to their assigned treatment plan. In the placebo group, patients will receive a placebo consisting of 250 mL of normal saline. In the treatment group, patients will receive a solution containing an LA injection of 600 mg (provided by Yabao Pharmaceutical Group Co.) dissolved in 250 mL of normal saline. To prevent exposure to light, both the LA and the placebo solutions will be wrapped in aluminium platinum paper. It is important that the intravenous drip time does not fall short of 30 min. Concomitant care include standard sepsis bundle treatment and other routine care. The critical care physicians are encouraged to adhere to the updated Surviving Sepsis Campaign guidelines,^7^ although the final decision is at the discretion of the physicians as per institutional guidelines. The number and percentage of patients in both the treatment and placebo groups who deviated from the sepsis bundle treatment will be documented.

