This study design possesses several strengths. First, the utilisation of a large sample size in this RCT can enhance our understanding of the efficacy of LA, a commonly used adjuvant drug in sepsis treatment lacking evidence-based support. Second, the exclusion of terminal disease as a confounding factor is addressed in this study. Sepsis can occur in patients already succumbing to other causes (eg, terminal cancer), and inherent mortality associated with sepsis is a characteristic of the syndrome itself. Third, the hypothesis that LA provides organ protection against sepsis injury is backed by substantial evidence from both animal and human research. Nonetheless, there are certain limitations that should be acknowledged. First, the relatively limited number of participating centres may introduce selection bias, potentially affecting the generalisability of the research findings to other contexts or settings. Second, this study design adopts a single-blind approach, which could introduce diagnostic bias by the investigators, potentially resulting in treatment imbalances between the control and treatment groups.

In conclusion, the ALIS study is a large-sample-sized, multicentre, single-blinded, randomised, parallel-group, placebo-controlled trial in China. It is designed based on robust evidence from basic and clinical studies. The anticipated outcomes of this trial have the potential to offer evidence-based recommendations for sepsis prevention in critically ill patients.

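### One published block size of 8 within each site makes some allocations predictable to anyone there who knows the earlier ones, and the protocol contradicts itself on whether investigators do

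*Protocol article*

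**What the plan says.** The Allocation section describes a "computer-generated block randomisation schedule with a block size of 8, stratified by site". It adds: "Each block will consist of four patients receiving the LA injection and four patients receiving a placebo". Assignment is central: "The randomisation centre, through net verification, will assign the screened patients at each hospital in a random manner". On disclosure it says: "The randomisation method and block size will not be blinded until all data analysis is completed".

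On blinding, the list of strengths and limitations after the trial registration states: "This trial follows a single-blind study design rather than a double-blind design". The Introduction and the study design section also call the trial single-blind. No section lists who is blinded. The Discussion gives as a limitation that "this study design adopts a single-blind approach, which could introduce diagnostic bias by the investigators", and adds that treatment could then differ between the groups.

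The code-break paragraph under Allocation reads differently. It restricts code breaks to exceptional cases, requires each one to be reported, and says: "Investigators are encouraged to consult with medical advisors if they believe that unblinding is necessary". Under Interventions, "both the LA and the placebo solutions will be wrapped in aluminium platinum paper", and the reason given is protection from light.

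**The concern.** With permuted blocks of one known size, a person who sees each allocation can count down the block. Once four patients in a block have gone to one arm, every remaining place in it is known. Central web assignment hides the list but does not prevent this inference. The statement that investigators take no part in data collection concerns data, not enrolment.

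The people who could use such knowledge are those who enrol. Under Recruitment a coordinator at each centre screens, and under Consent and assent the clinical investigator obtains consent. The eligibility criteria leave room for judgement: whether an infection source can be controlled, whether another condition is life-threatening, and when within a 48-hour window a patient is entered. A patient could be declined or delayed according to the expected arm. The primary endpoint, 28-day all-cause mortality, resists biased assessment, but it does not resist biased selection of who enters each arm.

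**Working it through.** The document gives no predictability figure to reproduce. All figures below are for an observer who knows the block size and every earlier allocation at the site, in order.

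**Inputs.** Block of 8, four per arm, stratified by site (Allocation); 352 patients and eight hospitals (Abstract, Table 1). Equal recruitment, 352 / 8 = 44 per site, is an assumption.

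**1. Certain allocations by place in the block.** There are C(8,4) = 70 equally likely blocks. Place k is certain when all four patients of one arm fall in the first k − 1 places, with probability 2 × C(k − 1, 4) / 70:

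| Place | Probability that it is certain |
|---|---|
| 1 to 4 | 0 |
| 5 | 2/70 = 2.9% |
| 6 | 10/70 = 14.3% |
| 7 | 30/70 = 42.9% |
| 8 | 70/70 = 100% |

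The sum is 112/70 = 1.6 per block, or 1.6 / 8 = 20.0%. The closed form agrees: with m = 4 per arm, 2m/(m + 1) = 8/5 = 1.6.

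**2. Number of patients.** If every block is completed: 0.20 × 352 = 70.4. With 44 per site there are five complete blocks and four places of a sixth. The complete blocks give 5 × 1.6 = 8.0 and the first four places of the sixth give 0. Over eight sites that is 64 of 352 = 18.2%.

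**3. Best guess.** The observer guesses the arm with more places left, and a tie counts one half. Expected correct guesses per block are m + (2^(2m)/C(2m, m) − 1)/2 = 4 + (256/70 − 1)/2 = 5.33, and 5.33 / 8 = 66.6%. Enumerating all 70 blocks gives the same value.

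**4. Effect of hidden, varied sizes.** This was simulated with 44 patients per site and 2,000 replicates. The observer knows the set of possible sizes and all past allocations, but not the size of the current block.

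| Block sizes | Certain | Best guess correct |
|---|---|---|
| 8 only | 18.2% | 65.8% |
| 4, 6, 8 | 2.4% | 67.6% |
| 6, 8, 10 | 1.7% | 65.9% |

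Varying the size removes most of the certainty. It does not remove the guessing advantage of someone who sees past allocations.

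**The case against.** The strongest objection is that nobody is stated to be unblinded. Single-blind is not defined, and that investigators know the arm is only inferred from the authors' own limitation. The code-break text points the other way. Data collection and management also gives site principal investigators full information only with permission. This stands: the predictability figures depend on a question that the document answers in two ways. If investigators are blinded, predictability is much lower.

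Second, the sentence that the block size will not be blinded until analysis is complete is probably garbled, and may mean that it will not be disclosed until then. A reader might infer a plan to reveal the block size to sites. The text does not support that, and publication in the article does not show that sites knew the size when recruitment began on 26 August 2021. What remains is that the sentence is wrong under the intended reading and that the size is now public.

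Third, one allocation in five is a ceiling for a fully informed observer. The study design section names general, neurological, surgical and emergency ICUs, so following the sequence across units at one hospital may be difficult. This also stands.

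Fourth, baseline SOFA and APACHE II scores are collected, so measured imbalance could be examined and adjusted for. That helps only in part, because selection on unrecorded features would remain.

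**Conclusion.** The point holds as a risk. The protocol fixes and publishes a single block size within site, in a trial called single-blind whose own limitations imply that investigators may know the arm. For an observer with the block size and the full ordered allocation history of the site, 20% of allocations in complete blocks are certain (18%, about 64 patients, at an assumed 44 per site), and the best guess is right about 66% of the time.

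A reader might go further and infer that investigators are unblinded by design, that one in five allocations really is foreseen, or that the mortality comparison is biased. The document supports none of these: the first is inferred and contradicted, the second needs knowledge that site staff may not have, and nothing shows that enrolment has been steered. What is secure under either reading is that the blinding statements conflict and the disclosure sentence needs correcting.

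**What to change.** 1. For all blocks not yet released, let the randomisation centre use randomly varied block sizes (for example 6, 8 and 10, or 4, 6 and 8) and withhold them from sites until database lock.
2. Correct the disclosure sentence under Allocation to say this.
3. State who is blinded, and reconcile the single-blind statements with the code-break text.

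The cost is one amendment, a regenerated list for the unreleased part, and slightly more complex list handling. Imbalance within a site cannot exceed half the largest block: four patients with sizes up to 8, as now, or five with sizes up to 10. How many blocks remain is not known from the article. If none remain, items 2 and 3, with item 2 reworded to describe what was actually done, are still needed so that readers can judge allocation concealment.

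Because varied sizes leave guessing accuracy near 66-68%, an optional further step is to withhold each allocation from those who screen and enrol, where roles can already be separated. That has a staffing cost of its own at each of the eight sites.
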